### Data analysis

Data will be described as the mean and SD or median and IQR according to the data distribution. The frequency of ICU mortality per group with a risk difference and 95% CI and a corresponding OR and 95% CI will be reported. Kaplan–Meier analysis will be used to analyze the rate of death in a time-to-event analysis, and the survival difference will be tested using a Cox proportional hazards model. For univariate analysis, the difference will be compared between the UFH and placebo groups using the Mann–Whitney U test or 𝜒2 and Fisher’s exact test. A two-tailed *p* value <0.05 was considered statistically significant. All statistical analyses were conducted using SPSS 22.0 and GraphPad Prism 9.0 software (GraphPad Software, San Diego, CA). The register number, participants lost due to follow-up, and violations of the protocols will be reported. The missing data will be handled with multiple imputation method.

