### Randomization and allocation concealment

There are 20 participant ICUs with 20 investigators. The eligible participants who meet the inclusion criteria and provide informed consent will be randomized using a software-generated randomization number. Each ICU is assigned an independent, random numeric table by the center primary investigator. There are equal numbers of 1 and 2, which represent the control group (sterile saline) and the heparin group (UFH), respectively. Once an eligible participant has enrolled, the independent drug administrators will obtain group information from the assigned table according to the chronological order of recruitment and assign the study drugs to the nurses for administration.

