### Outcomes

The primary outcome of the study is ICU mortality. The secondary outcomes include the following: a) 28-day all-cause mortality; b) improvement in SOFA scores; c) improvement in the Japanese Association for Acute Medicine (JAAM) and International Society on Thrombosis and Hemostasis (ISTH) scores; and d) bleeding risks during the study period. The daily bleeding monitor sheet is shown in Table 2.

**Table 2 Tab2:** Daily bleeding monitor sheet

Classification	Manifestation	Intervention
Major bleeding	- Intracranial bleeding - Gastrointestinal hemorrhage (haematemesis, tarry stool) - Severe nose bleeding - Other fatal bleeding	Stop infusion of study drugs and recorded in the CRF
Minor bleeding	- Mild gum bleeding - Mild epistaxis - Airway mucosa bleeding - Puncture site bleeding - Bruise or skin purpura	Attending physicians monitor and make a decision

*CRF*, case report format

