### Sample size calculation

The sample size calculation was based on a previous study [18]. With a significance level of 0.1, test power of 80%, mortality of severe sepsis in the control group of 42.1%, mortality in the heparin group of 31.7%, and a 12% dropout rate, a total of 600 participants (300 in each group) will be needed.

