### Data collection and management

Upon enrollment, baseline data, including epidemiologic characteristics, underlying disease, main diagnosis, Acute Physiology and Chronic Health Evaluation (APACHE II), SOFA, JAAM, and ISTH scores, infection sources and pathogens, and organ function indices, will be collected. General vital signs, infection indices (white cell count, neutrophil count, lymphocyte count, procalcitonin, C reactive protein, cytokines), organ function indices (cardiac, respiratory, hepatic, renal), coagulation variables (platelet counts, PT, INR, aPTT, fibrinogen, D-dimer, FDP, and antithrombin-III), and blood gas analyses will be recorded on the first, second, third, fifth and seventh days. Beyond that, treatment, including the volume of crystals, colloids, albumin and blood transfusion products, and urine volume, will be recorded every day. Outcomes, including ICU mortality, ventilator time, AEs/SAEs, and a follow-up visit on the 28th day, will be included.

All the data will be collected from the clinical electronic information system and recorded in the case report format (CRF). The data in the CRF recorded by researchers should be accurate, complete, and timely under the supervision and audit of two independent inspectors from the clinical research organization (CRO). All the CRFs will be recorded in an electronic document for statistical analysis. All participant centers were qualified by the National Medical Products Administration. The involved researchers complied with the Good Clinical Practice (GCP) guidelines during the study. All original documents will be stored in a locked site with restricted access at the Department of Critical Care Medicine of the First Affiliated Hospital of China Medical University for 10 years. The participant will be referred to by the participant code instead of the name in all the trial documents. Access will be granted to authorized person and the regulatory authorities to permit trial monitoring, audits, and reports.

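### The stated ICU-mortality comparison uses neither the ICU-specific allocation nor baseline severity: it is valid but less efficient than the collected data allow

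*Protocol article*

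**What the plan says.** All places are in the protocol article.

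- **Outcomes:** "The primary outcome of the study is ICU mortality", a binary endpoint.
- **Data analysis:** "The frequency of ICU mortality per group with a risk difference and 95% CI and a corresponding OR and 95% CI will be reported". Group differences are to be tested univariately by Mann–Whitney, chi-square or Fisher. The only model named is a Cox model for time to death, without covariates. No centre term, stratified test or baseline covariate appears, and the section does not refer to another document for them. The threshold is a two-tailed p "value <0.05 was considered statistically significant".
- **Randomization and allocation concealment:** "Each ICU is assigned an independent, random numeric table". Each list holds the two arms in equal number. With 20 ICUs this is stratification by ICU, although the article does not use the word. No block size is given.
- **Data collection and management:** the data to be collected at enrolment include "main diagnosis, Acute Physiology and Chronic Health Evaluation (APACHE II), SOFA, JAAM, and ISTH scores".
- **Table 3:** the ISTH and JAAM rows carry a D0 mark. The SOFA and APACHE II rows do not; they begin at D1, the first intervention day.

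**The concern.** Allocation is balanced within ICU, so part of the between-ICU variation in mortality is removed from the treatment contrast by design. A crude risk difference or chi-square test still counts that variation as noise, which makes its standard error slightly too large. A crude comparison also ignores how ill each patient was at entry, although scores built to predict death are being collected.

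What is at stake is efficiency. The trial has little power to spare at its stated 0.05 threshold, and an adjusted analysis would use data already on the case report form without recruiting anyone else. Naming the covariates in advance also prevents a later choice among many baseline variables.

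**Working it through.** **Inputs from the article.** Mortality 42.1% (control) and 31.7% (heparin); 12% dropout; 300 per arm, hence 300 × 0.88 = 264 per arm after dropout; 80% power; alpha 0.1 in Sample size calculation and two-tailed 0.05 in Data analysis.

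**Inputs assumed, because the article gives none.** The share of outcome variance explained by baseline variables (R²), the discrimination of a severity score (AUC), and the between-ICU SD on the log-odds scale.

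**1. Reproduce the stated sample size.** With p̄ = 0.369,

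n per arm = [z(1−α/2)·√(2p̄(1−p̄)) + z(1−β)·√(p₁(1−p₁) + p₂(1−p₂))]² / (p₁ − p₂)²

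At two-sided 0.10: (1.645 × 0.6824 + 0.842 × 0.6784)² / 0.104² gives 266 per arm. Dividing by 0.88 gives 303 per arm, 606 in total; multiplying by 1.12 gives 298 per arm, 596 in total. Both agree with the planned 600.

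**2. Crude power at two-sided 0.05.**

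Power = Φ{[0.104·√n − 1.960 × 0.6824] / 0.6784}

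- n = 264: (1.690 − 1.337)/0.6784 = 0.519, power 69.8%.
- n = 300: (1.801 − 1.337)/0.6784 = 0.684, power 75.3%.

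**3. Power after adjustment.** Baseline variables that explain a share R² of outcome variance act roughly like a sample of n/(1 − R²). For example, with R² = 0.20, 264/0.80 = 330 and power is 79.2%.

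| Assumed R² | 264 per arm | Gain (points) | Gain at 300 per arm (points) |
|---|---|---|---|
| 0.05 | 72.0% | 2.2 | 2.1 |
| 0.10 | 74.4% | 4.5 | 4.3 |
| 0.15 | 76.7% | 6.9 | 6.5 |
| 0.20 | 79.2% | 9.4 | 8.8 |
| 0.25 | 81.7% | 11.9 | 11.0 |
| 0.30 | 84.3% | 14.5 | 13.2 |

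At alpha 0.10 with 264 per arm, crude power is 79.8%. The gain is 3.6 points at R² 0.10 and 9.1 at R² 0.25, so the direction does not depend on which alpha is kept.

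**4. Simulation check.** 2,000 trials per setting, 20 equal ICUs with arms balanced inside each, one normal severity score, marginal mortality fixed at 42.1% and 31.7%. Results for 520 patients and an assumed between-ICU SD of 0.4:

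| Score AUC | Crude | ICU only (CMH) | Severity only | Severity + 20 ICU intercepts |
|---|---|---|---|---|
| 0.66 | 69.5% | 70.3% | 72.2% | 74.7% |
| 0.72 | 70.2% | 71.0% | 75.6% | 77.1% |
| 0.77 | 69.9% | 70.2% | 79.9% | 81.3% |
| 0.83 | 73.2% | 73.6% | 84.5% | 86.4% |

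The Monte Carlo standard error of each entry is about 1 point, but the methods share the same simulated trials. The severity score supplies nearly all of the gain; stratifying by ICU alone adds less than 1 point. Some of the last column's extra may not be real. With the between-ICU SD set to zero, the model with 20 fixed intercepts still showed up to about 1.5 points more power than severity alone, which suggests a slightly liberal test.

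**5. Type I error.** In 4,000 null trials with 600 patients and a larger assumed between-ICU SD of 0.7, the rejection rates were 4.3% (crude), 5.0% (CMH) and 5.4% (severity plus ICU intercepts). The Monte Carlo standard error is √(0.05 × 0.95/4,000) = 0.34 points. The crude test is therefore about 2 standard errors below nominal: mildly conservative at most.

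**The case against.** The strongest reply is that the article never calls its comparison unadjusted. A risk difference and an OR can both come from a model, the chi-square and Fisher tests are introduced only as univariate analysis, and covariate lists usually sit in an analysis plan that is not shown. It is true that nothing rules adjustment out. If the unseen plan already adjusts, one sentence saying so settles the point. But the article does state its estimates and tests, and as stated they use neither the allocation scheme nor the baseline data.

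Second, the size of the gain rests on inputs that the article does not supply. This stands. A reader might infer a firm loss of, say, 5 to 11 points, but that needs an R² of about 0.11 to 0.25, and nothing in the article fixes it there or shows how well these scores predict death in this population.

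Third, the stratification argument is small. This also stands: 0 to 1 point of power and slight conservatism. Since no block size is given, balance within an ICU is assured only when its list is completed.

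Fourth, a reader might blame the crude analysis for power of about 70%. The article does not support that. The shortfall comes from planning with "With a significance level of 0.1, test power of 80" per cent and then testing at 0.05, which takes power from 79.8% to 69.8% at 264 per arm. The 70% also assumes that 12% of patients drop out of the analysis; multiple imputation is planned, and with all 300 per arm crude power is 75.3%.

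**Conclusion.** The point holds as an efficiency improvement worth making, not as an error that invalidates the trial. The crude comparison is valid and slightly conservative. At two-sided 0.05 and 264 per arm, adjustment for baseline prognostic variables would raise power from about 70% by about 2 to 14 points, under an assumed R² of 0.05 to 0.30. Accounting for ICU alone is worth about 0 to 1 point; its main purpose is a standard error that matches the design.

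It would be too strong to say that adjustment rescues the power. It reaches 80% at 264 per arm only when R² is somewhat above 0.20 (79.2% at 0.20, 81.7% at 0.25). It is no substitute for resolving alpha 0.1 against 0.05: the crude test needs 337 per arm for 80% power at 0.05, or 766 in total with 12% dropout.

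**What to change.** 1. Reconcile Data collection and management, which lists SOFA and APACHE II among the data collected at enrolment, with Table 3, which first marks both at D1. Use a score as a covariate only if it was measured before the first dose; a D1 value could already reflect treatment.
2. Before unblinding, make the primary analysis a logistic model for ICU mortality with treatment, ICU (random intercept or stratum, rather than 20 fixed indicators), age and one pre-dose severity score.
3. Report the adjusted OR and a standardised marginal risk difference, each with a 95% CI. Keep the crude risk difference, OR and chi-square test as supporting analyses.
4. Resolve the two alpha levels separately.

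The cost is a few sentences of analysis text, plus a check that a pre-dose score exists for each patient. It needs no additional patients. One small drawback is that the adjusted OR is conditional on the covariates and so differs in meaning from the crude OR, which is why the marginal risk difference must stand beside it.

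### The only stated test that fits the SOFA, JAAM and ISTH score outcomes is unadjusted, although the enrolment scores are collected and adjusting for them would improve precision

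*Protocol article*

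**What the plan says.** The Outcomes section lists among the secondary outcomes "b) improvement in SOFA scores" and "c) improvement in the Japanese Association for Acute Medicine (JAAM) and International Society on Thrombosis and Hemostasis (ISTH) scores". It gives no time point or formula for improvement.

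Under Data collection and management, the enrolment data include the three scores: "SOFA, JAAM, and ISTH scores, infection sources and pathogens, and organ function indices, will be collected". In Table 3, JAAM and ISTH are marked from D0. The SOFA row has one mark fewer and appears to start at D1, the first day of the intervention period.

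The Data analysis section says of univariate analysis that "the difference will be compared between the UFH and placebo groups using the Mann–Whitney U test", or by chi-squared and Fisher's exact tests. The only regression model it names is the Cox model for survival. No analysis of covariance, ordinal model or repeated-measures model appears. The scores are not mentioned in the sentence on tests.

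**The concern.** A score measured before treatment usually predicts the same score afterwards. A two-group rank test that does not adjust for the enrolment value leaves that predictable variation in the comparison as noise.

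This is so under either reading of improvement. A change score carries the variation of both measurements and stays correlated with baseline. A follow-up score taken alone ignores baseline altogether.

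These are the trial's named efficacy outcomes on organ function and coagulation, and the Discussion rests its rationale on preventing DIC and improving the microcirculation. What is at stake is sensitivity: a real effect on the scores is more likely to be missed, and the estimate moves more with chance differences at baseline. The unadjusted test does not produce too many false positives.

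**Working it through.** **The plan's own figures.** The protocol gives no SD, effect size, correlation or power for the scores. Its only calculation is for mortality (42.1% versus 31.7%, significance level 0.1, power 80%, dropout 12%). The unpooled formula at two-sided 0.1 gives 264 per arm, and 264/0.88 = 300 per arm, or 600 in total, as stated. The point made here does not touch that figure. It supplies only the evaluable number per arm used below.

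**Variance.** Assume complete, roughly normal scores with the same SD (set to 1) at both times and correlation r. The documents do not give r, so a range is shown.

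- Change score: 2(1 − r)
- Follow-up score alone: 1
- Adjusted for baseline: 1 − r²
- Adjusted relative to change: (1 − r²) / [2(1 − r)] = (1 + r)/2
- Adjusted relative to follow-up alone: 1 − r²

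| r (assumed) | Adjusted / change | Adjusted / follow-up alone |
|---|---|---|
| 0.3 | 0.91/1.40 = 0.65 | 0.91 |
| 0.5 | 0.75/1.00 = 0.75 | 0.75 |
| 0.7 | 0.51/0.60 = 0.85 | 0.51 |
| 0.8 | 0.36/0.40 = 0.90 | 0.36 |

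Both ratios are below 1 for every r strictly between 0 and 1.

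**Power without deaths.** At two-sided 0.05 and 264 per arm, suppose the change-score comparison has 80% power. The adjusted comparison then has 93.5%, 89.9% and 86.0% at r = 0.3, 0.5 and 0.7. If the follow-up comparison has 80%, the adjusted one has 83.6%, 89.9% and 97.5%.

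A simulation (4,000 runs, normal scores, effect set to give the change-score comparison 80%) agrees:

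| r | Mann–Whitney on change | Mann–Whitney on follow-up | Analysis of covariance |
|---|---|---|---|
| 0.3 | 77.8% | 89.0% | 92.8% |
| 0.5 | 78.6% | 77.2% | 90.0% |
| 0.7 | 79.1% | 56.5% | 86.5% |

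**Power with deaths ranked worst.** The protocol assumes 31.7% to 42.1% mortality but gives no death rate by day 7, so 20% and 35% are taken for illustration. Further assumptions: 300 per arm, integer scores with SD 3.5, an effect of 0.2 SD on the score, no effect on death, and log-odds of death rising by 0.5 per baseline SD. There were 1,500 replicates.

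| Deaths | r | Mann–Whitney on change | Rank analysis of covariance on day-7 score |
|---|---|---|---|
| 20% | 0.3 | 25% | 35% |
| 20% | 0.5 | 31% | 38% |
| 20% | 0.7 | 47% | 43% |
| 35% | 0.3 | 13% | 17% |
| 35% | 0.5 | 19% | 22% |
| 35% | 0.7 | 25% | 21% |

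The gain shrinks, and at r = 0.7 the order reverses slightly. The two columns analyse different outcomes, change and day-7 score. A re-run under the same assumptions gave the same pattern. When the same outcome was analysed with and without the enrolment score, adjustment never lost appreciable power, and null rejection rates stayed near 5%. For a change score with deaths ranked worst, adjustment added almost nothing.

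**The case against.** The strongest case against is that the protocol never assigns Mann–Whitney to these scores. It gives a generic list of univariate tests and does not define improvement, and adjustment of secondary outcomes is often left to a statistical analysis plan, which is not shown here. A reader might infer that the protocol expressly commits to an unadjusted rank test of change scores. The text does not support that. What stands is narrower: the section does state tests, only one of them fits a score, and no adjusted model stands beside it. It is therefore fair to ask for that wording to be changed.

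Second, an unadjusted rank test is valid under randomisation, and chance imbalance is already covered by its type I error rate. That is right. This is a loss of efficiency, not a bias.

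Third, a reader might infer that the gain is free and certain, or take the no-death power figures as what adjustment would yield here. Neither is supported. The correlation is assumed, the scores are bounded and ordinal, and the gain shrinks or disappears once deaths are ranked worst. The time point, the rule for deaths and the handling of early discharge are separate choices about the outcome. Adjustment does not settle them.

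**Conclusion.** The point holds as a matter of precision in secondary outcomes. The only stated test that fits the score outcomes ignores an enrolment value that the protocol says is collected.

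For complete, roughly normal scores and r from 0.3 to 0.7, adjustment cuts the variance by 15% to 35% against a change score and by 9% to 49% against the follow-up score alone. These figures rest on assumed correlations and on equal SDs at the two times. With deaths ranked worst the benefit is smaller and its size cannot be fixed from the document. What can be said is that adding the enrolment score to the analysis of a given outcome did not cost appreciable power in the settings examined.

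For SOFA there is a prior condition. If the first value is taken on D1, after the infusion may have begun, it is not a clean baseline covariate. JAAM and ISTH are marked at D0 and do not have this problem. ICU mortality and the sample size are not affected.

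**What to change.** In Data analysis, state that the main between-group comparison of each score outcome is a model adjusted for the enrolment value of the same score and for centre: analysis of covariance, rank analysis of covariance or proportional odds. Centre belongs in the model because each ICU has its own randomisation table. Keep the Mann–Whitney test as a sensitivity analysis.

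Reconcile the SOFA row of Table 3 with Data collection and management, so that the SOFA covariate is clearly a value taken before study drug starts.

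The cost is small: a little more analysis work and a model assumption to check. No new data are needed beyond the enrolment scores the text already says are collected. The article describes recruitment as open and statisticians as blinded, so on that footing the change can still be prespecified.

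### The multiple-imputation rule does not separate scores missing in living patients from SOFA, JAAM and ISTH scores that do not exist because the patient died

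*Protocol article*

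**What the plan says.** The protocol article deals with missing data in one sentence at the end of Data analysis: "The missing data will be handled with multiple imputation method". It sets no limit by variable, time point or reason for absence.

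Under Outcomes, the secondary outcomes include "improvement in SOFA scores" and "improvement in the Japanese Association for Acute Medicine (JAAM) and International Society on Thrombosis and Hemostasis (ISTH) scores". No time point is attached to either. Table 3 schedules all three scores on D1, D2, D3, D5, D7 and at ICU discharge. Data collection and management says that the underlying measurements "will be recorded on the first, second, third, fifth and seventh days".

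On mortality, "The primary outcome of the study is ICU mortality". The sample size assumes "mortality of severe sepsis in the control group of 42.1"% and "mortality in the heparin group of 31.7"%.

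For between-arm comparisons, Data analysis names the Mann-Whitney, chi-square and Fisher tests. Nothing in the article says how death enters the score outcomes: there is no worst rank, no assigned score and no restriction to survivors.

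**The concern.** A score absent because a sample was lost or a visit was missed has a true value that was not observed, and imputation can reasonably estimate it. A score scheduled after death has no true value. An imputation model fitted to patients with observed scores would give the dead the recovery expected of survivors with similar earlier values.

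This trial is designed to detect a difference in mortality. If its hypothesis is right, death cuts off more scores in the control arm than in the heparin arm. The arm that loses more of its sickest patients would have them replaced by survivor-like values, while the other arm keeps comparable patients alive with their real, poor scores. The score comparison could then lean toward the arm with more deaths. At stake is the reading of the secondary score outcomes, not the mortality result.

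**Working it through.** **1. The plan's own figure.** Inputs from Sample size calculation: control 0.421, heparin 0.317, significance level 0.1 (sidedness not stated; taken as two-sided), power 80%, dropout 12%. With pooled proportion (0.421 + 0.317)/2 = 0.369:

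n per arm = [1.645·√(2·0.369·0.631) + 0.842·√(0.421·0.579 + 0.317·0.683)]² / 0.104² ≈ 2.868/0.01082 ≈ 265.1, so 266.

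Dividing by 0.88 gives 303 per arm (606 in total); multiplying by 1.12 gives 298 (596). Both agree with the stated 600, so these mortality rates are the ones the design rests on.

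**2. Deaths implied.** 300 × 0.421 = 126.3 and 300 × 0.317 = 95.1. The total is 221.4 of 600, or 37%. If the rates are read as ICU deaths, none of these patients can have a score at live ICU discharge. How many lack a D7 score depends on when they die, which the article does not say.

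**3. Effect on SOFA improvement (simulation).** All inputs here are assumptions, not figures from the article:
- 300 patients per arm, 300 replicates, no effect of treatment on any patient's SOFA.
- Baseline SOFA is normal with mean 10 and SD 3. A latent course u is normal with mean 0 and SD 2.
- D3 = baseline + u − 0.5 + noise (SD 1.5). D7 = baseline + 1.3u − 2 + noise (SD 1.5).
- Risk of death = k·[0.15·(baseline − 10) + 0.35·u] + logistic noise. The patients at highest risk die, up to the set proportion. k = 0 means that death is unrelated to severity.
- D7 is imputed within arm from baseline and D3, fitted on survivors, with 10 imputations.
- The higher mortality is placed in the treated arm. Swapping the arms reverses the sign.

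Difference in mean improvement, treated minus control (positive favours the arm with more deaths):

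| k | Imputed, all deaths before D7 (42.1% v 31.7%) | Survivors only, same | Death scored 24, same | Imputed, half before D7 (21% v 16%) | Survivors only, same | Death scored 24, same |
|---|---|---|---|---|---|---|
| 0 | 0.00 | 0.01 | −1.63 | −0.01 | −0.01 | −0.81 |
| 1 | 0.06 | 0.14 | −1.58 | 0.02 | 0.07 | −0.72 |
| 2 | 0.12 | 0.23 | −1.54 | 0.05 | 0.11 | −0.68 |
| 4 | 0.19 | 0.30 | −1.54 | 0.08 | 0.15 | −0.65 |

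A second simulation used a thinner imputation model (baseline SOFA and arm only) and assumed D7 mortality. It agrees in direction. The arm with fewer deaths looked 0.14 points worse at 24.2% v 17.6%, and 0.17 worse at 24.2% v 15.2%. An arm with more deaths (31.7% v 24.0%) looked 0.16 better.

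**4. Scale.** With an assumed SD of change of 3 to 4 points, the standard error of the difference at 300 per arm is SD × √(2/300), or 0.24 to 0.33. A shift of 0.05 to 0.2 is below one standard error.

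**The case against.** The strongest reply is that this is detail for the analysis plan. The article is condensed, its sentence names a method without a model or scope, and the sentence before it concerns loss to follow-up and protocol violations. Missing data may therefore mean incomplete follow-up only. A reader might infer that the plan announces imputation for dead patients. It does not say so; that follows only from the unrestricted wording, and a fuller plan may qualify it. What remains is that the rule as stated covers these outcomes and nothing in the article excludes them.

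A reader might also infer that most missing scores will be due to death, or that 221 counts the missing D7 scores. Neither is supported. The timing of deaths is not given. Live discharge before D7 is possible, because only patients with an expected ICU stay under 48 h are excluded and participation is required only while in the ICU.

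A third tempting reading is that all three outcomes will move the wrong way whenever heparin saves or costs lives. The shift needs death to depend on severity, it is small, and JAAM and ISTH were not simulated.

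Finally, ranking death as worst changes the question. In the table, scoring death as 24 produces differences of −0.65 to −1.63 with no true score effect, much larger than the imputation shift. This objection stands. It is a reason to label the outcome openly, not a reason to impute scores for the dead.

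**Conclusion.** The concern holds as a conditional one about the secondary score outcomes. Applied as written, the rule gives dead patients survivor-like scores and removes any penalty for death. If death depends on severity, it also moves the SOFA comparison modestly toward the arm with more deaths: about 0.06 to 0.19 points if all planned deaths precede D7, and 0.02 to 0.08 if half do. If death is unrelated to severity the shift is about zero. These sizes rest on assumed score distributions, an assumed link between death and severity, and an assumed timing of deaths. For JAAM and ISTH the mechanism is the same but the size is unknown.

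Restricting imputation is not enough alone. The survivors-only comparison leans the same way, and in this simulation leaned further (0.14 to 0.30 with all deaths before D7). Death has to enter the comparison explicitly. ICU mortality, 28-day mortality and the sample size are untouched, so this is a worthwhile improvement and not a threat to the trial's main conclusion.

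**What to change.** Add to Data analysis, before unblinding:

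- Multiple imputation applies only to values missing in patients alive at the time point concerned. Scores scheduled after death are not imputed.
- Improvement in SOFA, JAAM and ISTH is compared at one prespecified time point, for example D7. Death before that time ranks as the worst result, and the arms are compared with the Mann-Whitney test already planned. This needs a rank for death, not an invented score.
- Change among survivors is reported as descriptive only.

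The cost is two or three sentences; no new data and no change to the sample size are needed. The downside is that each score outcome becomes a composite partly driven by mortality, which is already the primary outcome and a secondary one. It must be labelled as a composite and read beside the mortality results, and a difference in it must not be presented as evidence of better organ function or coagulation among survivors.
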